## 5. OUTCOME MEASURES

**Time Points:** Baseline (Pre) and Week 3 (Post-Intervention).

### 1. ASIA Impairment Scale (ISNCSCI):

- **Motor Score (LEMS):** 5 key muscles per leg (0-5 scale). Max = 50.
- **Sensory Score:** Light Touch and Pin Prick at 12 key points per leg. Max = 48 each.

### 2. Assessment of Movement Attempt (AMA):

- Structured interview rating the **Intensity** (1-6) and **Frequency** (1-6) of the attempt to move the paralyzed limb.

## 6. CONFIDENTIALITY AND DATA SECURITY

### 6.1. Data Protection:

- All participant data will be coded to ensure anonymity.
- Paper records will be stored in locked cabinets at the Faculty of Public Health.
- Digital data will be stored on password-protected computers accessible only to the research team.

#### 6.2. Access to Data:

- Only the Principal Investigator ([name] [name]) and authorized co-investigators will have access to the raw data.
- Data will be retained for 3 years post-study for verification purposes and then destroyed.

## 7. ETHICAL CONSIDERATIONS

- **Informed Consent:** Written informed consent will be obtained from all participants in Arabic (their native language). The consent form explains the study purpose, procedures, risks, and the right to withdraw at any time. (See attached *Consent Form*).
- **Safety Monitoring:** A senior research specialist will monitor all sessions. Any adverse events (e.g., skin redness, dizziness) will be recorded and reported immediately. If a patient reports severe symptoms (score 5/10 on the safety questionnaire), they will be withdrawn from the study.
- **Risk/Benefit Analysis:** The risks of tDCS (mild skin irritation, headache) are minimal and transient. The potential benefits (motor recovery) are significant for this patient population.

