### Hypothesis:

We hypothesize that the NEUROM method, especially when combined with anodal tDCS, will induce greater sensorimotor recovery than conventional therapy alone in patients with chronic paraplegia.

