### 3.3. Randomization:

Participants will be randomly assigned into three groups using a web-based random number generator ([www.random.org](http://www.random.org)) in a 1:2:2 ratio:

1. **Reference Group ( $n = 10$ ):** Conventional physical therapy.
2. **NEUROM Group ( $n = 20$ ):** Neural Motor Recruitment protocol.
3. **NEUROM + tDCS Group ( $n = 20$ ):** NEUROM protocol + tDCS.

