## 4. GENERAL EXPERIMENTAL PROCEDURE

### 4.1. Conventional Rehabilitation Program (Reference Group)

Patients will receive a standardized conventional program including:

- Passive and active mobilization.
- Strengthening and endurance exercises.
- Neuromuscular facilitation techniques.
- **Dosage:** 5 sessions/week for 3 weeks.

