### 4.2. Neural Motor Recruitment (NEUROM) Method

This closed-loop protocol consists of two phases:

- **Phase 1 (Week 1):** Daily Motor Imagery (MI) training combined with 20 minutes of static stretching (hamstrings/soleus).
- **Phase 2 (Weeks 2-3):** Active NEUROM sessions.
  - **Visual:** Patients view a 5-minute video of feet performing dorsi- and plantarflexion on a large screen (43-inch, 3.5m distance).
  - **Cognitive:** Audio instructions guide the patient to perform Kinesthetic Motor Imagery ("Imagine yourself performing the movement...").
  - **Sensory:** Concurrent peripheral sensory stimulation.

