### 4.3. Transcranial Direct Current Stimulation (tDCS)

- **Device:** Starstim NE wireless neurostimulator (Neuroelectronics®, Barcelona).
- **Montage:** Bi-hemispheric (C3/C4). Alternating anode/cathode placement on Left/Right M1 daily.
- **Parameters:** 1 mA intensity, 20 minutes duration, 7-second ramp.
- **Safety:** A neurologist will screen patients for contraindications. A specific questionnaire for adverse effects (headache, skin irritation) will be administered before and after each session.

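### The 5/10 safety rule ends study participation rather than study treatment, so a patient who meets it before Week 3 would, on a plain reading, have no outcome

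*Protocol*

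**What the plan says.** Section 7 of the Protocol (Ethical Considerations, Safety Monitoring) gives the rule: "If a patient reports severe symptoms (score 5/10 on the safety questionnaire), they will be withdrawn from the study". It names no arm. The same item says "A senior research specialist will monitor all sessions".

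Section 5 (Outcome Measures) gives the time points as "Baseline (Pre) and Week 3 (Post-Intervention"; there is no interim assessment and no later one. The outcomes are the ISNCSCI motor and sensory scores and the Assessment of Movement Attempt (AMA).

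The only safety questionnaire that the Protocol describes is in Section 4.3, on tDCS: "A specific questionnaire for adverse effects (headache, skin irritation) will be administered before and after each session". Section 3.3 randomises 20 of 50 patients to "NEUROM protocol + tDCS". The hypothesis in Section 2 is that NEUROM, "especially when combined with anodal tDCS, will induce greater sensorimotor recovery than conventional therapy alone".

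The Protocol does not separate stopping treatment from leaving the study, and it does not say that a withdrawn patient is still assessed. Section 7 refers to an attached consent form, which is not at hand.

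**The concern.** A safety rule has to stop the treatment that may be causing harm. It does not have to stop measurement. As worded, this rule does both, and it can operate throughout the treatment weeks, before the single post-baseline visit.

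Outcomes would then go missing because of how patients tolerated treatment, which is an event after randomisation. If that happens mainly in one arm, the patients left in that arm are no longer the group that was randomised, and the comparisons behind the combination hypothesis are affected. An analysis plan can choose a method for missing values but cannot replace an assessment that the conduct rule prevented. The point therefore concerns what the Protocol fixes, not what it may leave to an analysis plan.

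**Working it through.** **Group sizes.** At 1:2:2, 50 × 1/5 = 10, 50 × 2/5 = 20 and 50 × 2/5 = 20, as Section 3.3 states. The Protocol gives no dropout rate, event rate, SD or power, so no further figure can be reproduced.

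**Does the loss follow from the text?**
1. The rule applies at a score of 5/10, and the questionnaire is given before and after each session. It can therefore be triggered from the first session to the last.
2. The consequence is withdrawal from the study.
3. The only outcome visit after baseline is at Week 3.
4. So a patient who meets the threshold before that visit has, on a plain reading, no post-baseline value. A score at or near the last session need not cost the outcome.

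**Which arm?** The questionnaire is described only under tDCS, which points to NEUROM + tDCS. That is an inference. Section 7 names no arm, and NEUROM itself includes "Concurrent peripheral sensory stimulation", so the rule may reach the other NEUROM arm too.

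**How many outcomes? (assumed inputs)** The number of tDCS sessions is not stated. Take n = 10 (Weeks 2 and 3 at five a week) or n = 15 (three weeks at five a week). The rate of "5 sessions/week for 3 weeks" is given only for the reference group. Assume a chance p per session of a 5/10 score, the same for all patients and sessions, and let last-session events keep their outcome.

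- Expected losses among 20 = 20 × (1 − (1 − p)^(n−1))
- P(no loss) = (1 − p)^(20(n−1))

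| p | n = 10: expected lost | n = 10: P(none) | n = 15: expected lost | n = 15: P(none) |
|---|---|---|---|---|
| 0.1% | 0.18 | 0.84 | 0.28 | 0.76 |
| 0.5% | 0.88 | 0.41 | 1.36 | 0.25 |
| 1% | 1.73 | 0.16 | 2.63 | 0.06 |

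**How far could the result move?** Let D be the mean difference in outcome between patients who stay and patients withdrawn, assumed to lie between −1 and +1 SD. With w of 20 lost, the completers' mean differs from the full-arm mean by (w/20) × D. The standard error of the difference, in SD units, is √(1/(20 − w) + 1/20) against NEUROM and √(1/(20 − w) + 1/10) against conventional therapy.

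| w | Largest shift (SD) | SE vs NEUROM | Shift/SE | SE vs conventional | Shift/SE |
|---|---|---|---|---|---|
| 1 | 0.05 | 0.320 | 0.16 | 0.391 | 0.13 |
| 2 | 0.10 | 0.325 | 0.31 | 0.394 | 0.25 |

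If both NEUROM arms lose equal numbers with the same D, the shift in their difference is zero. With 2 lost against 1, it is at most 0.10 − 0.05 = 0.05 SD; the SE is √(1/18 + 1/19) = 0.329 and the ratio 0.15.

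**Power.** For an assumed effect of 0.8 SD at two-sided 5%, losing as many as 4 of the 20 tDCS patients lowers power from 54% to 51% against conventional therapy and from about 72% to about 67% against NEUROM. Precision is hardly affected; the issue is possible bias.

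**The case against.** The rule is one sentence in a short protective item, and withdrawal from a study is often shorthand for stopping the intervention. Nothing in the Protocol says that a withdrawn patient will be turned away at Week 3 or that data will be discarded. The consent form might settle the meaning. This stands as a limit on confidence. It does not remove the point, because staff who apply the sentence literally would not hold the visit.

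The size rests entirely on assumed inputs. What the Protocol does say points to few events: 1 mA stimulation, screening by a neurologist, and risks described as minimal and transient. If high scores cluster in a few sensitive patients, the same average rate loses fewer patients than the table shows. The shift figures also presume a comparison of completers, which the Protocol does not specify. All of this stands and keeps the point minor.

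A reader might infer that the trial's result will be biased, or biased in favour of tDCS. The documents do not support that: the number of events may be zero, the sign of D is unknown, and there is no bias if tolerance is unrelated to recovery. A reader might also infer that the losses can fall only on the tDCS arm, but Section 7 does not limit the rule to it.

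Finally, one might argue that only tDCS should stop and that NEUROM should go on. That would replace an automatic stop with a judgement after severe symptoms, and would leave some patients in the combined arm receiving NEUROM alone. It is a separate safety and design choice, and keeping the outcome does not require it.

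**Conclusion.** The point holds as a minor one, with medium confidence. Read plainly, the safety rule ends data collection for a patient who meets the threshold before the only post-baseline visit, for a reason linked to tolerance of treatment. Any loss probably falls mainly on NEUROM + tDCS, where each is 5% of the arm.

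Under the stated assumptions the expected loss in that arm ranges from about 0.2 to 2.6 patients, and one or two losses move a comparison by at most about a third of a standard error. The direction is unknown. None of these figures shows that the trial's conclusion would change. The case for amending is that the loss is avoidable at almost no cost and cannot be repaired afterwards.

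**What to change.** Keep the 5/10 threshold and the automatic stop. In Section 7, replace the clause that orders withdrawal with:

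*Study treatment will be stopped; unless the patient withdraws consent or assessment is unsafe, the patient will still be invited to the scheduled Week 3 ISNCSCI and AMA assessments, and those data will be kept in the randomised group.*

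The cost is one sentence by amendment, plus holding an already scheduled visit for patients who stopped treatment. It needs no extra patients, visits or questionnaires. If the investigators always meant to stop treatment only, the sentence simply states that intent. Whether NEUROM may continue without tDCS is left to the investigators and is not part of this change.
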